# B1. PURPOSE OF PROTOCOL

| To evaluate the effects of Tai Chi—a mind-body exercise––on age-related loss of physiological complexity (using fractal and entropy based measures), and to understand the relationship between complexity, function and adaptability, we will conduct a two-arm prospective randomized clinical trial. Our overarching goal is to evaluate if six months of Tai Chi training, compared to a waitlist control receiving standard medical care, can enhance physiological complexity and adaptability in older Tai Chi-naïve adults. Secondary goals of the study are to characterize the relationship between complexity biomarkers, measures of function, and resilience. This pilot study will inform a future more definitive trial by providing information on recruitment and retention, compliance, dose-dependent effects, preliminary estimates of effect size, and the optimal biomarkers of complexity, function, and adaptive capacity.    **Specific Aim #1: To determine if 6 months of Tai Chi training can increase complexity, function, and adaptive capacity of multiple physiological systems in older healthy adults.** Sixty healthy older adults (50-79y) naïve to Tai Chi will be recruited from the Boston community and randomized to either 6 months of Tai Chi training or to a waitlist control. Measurements of complexity, adaptive capacity, and function will be assessed at baseline, 3, and 6 months. Dynamics of cardiovascular (heart rate), balance (center-of-pressure displacement), and locomotor (gait stride interval) systems will be quantified using indices derived from two complementary analytic methods developed by members of our team––detrended fluctuation analysis^26^ and multi-scale entropy.^6^ Function will be characterized by exercise capacity, clinical measures of balance, lower and upper extremity strength, cognitive function, and health related quality of life. Adaptability of multiple physiological systems will be assessed using common perturbations including: heart rate responses to posture change, center of pressure (i.e. balance) responses to a dual cognitive task and closed eyes, and c) gait responses to dual cognitive task. In addition to informing the feasibility of a future trial, outcomes will provide preliminary data to evaluate the following hypotheses.  ***Hypotheses*** *Compared to the control group:*  *H.1.a) Those who participate in Tai Chi will exhibit higher levels of complexity across all measured physiological systems;*  *H.1.b) Those who participate in Tai Chi will exhibit higher levels of physical and cognitive function;*  *H.1.c) Those who participate in Tai Chi will exhibit higher levels of adaptive capacity;*  *H.1.d) The magnitude of the effects of Tai Chi on physiological complexity, function and adaptive capacity in healthy older adults will be positively correlated with age.*  **Specific Aim #2: To determine the relationships between biomarkers of physiological complexity, conventional measures of function and adaptive capacity.** Statistical regression models will be used to determine relationships, both at baseline and overtime, between a) complexity biomarkers and measures of physical and cognitive function, and b) complexity biomarkers and adaptive capacity. Elucidating these relationships will further inform the interpretation of complexity biomarkers and provide insights into underlying component mechanisms contributing to complex physiological dynamics.  ***Hypotheses*** *At baseline:*  *H.2.a) Measures of complexity are positively correlated with physical and cognitive function;*  *H.2.b) Measures of complexity are positively correlated with adaptive capacity.*  *Over time:*  *H.2.c) Changes in complexity are positively correlated with changes in physical and cognitive function;*  *H.2.d) Changes in complexity are positively correlated with changes in adaptive capacity.*  **Specific Aim #3: To determine cross-sectionally if long-term Tai Chi training (> 5 years) is associated with greater complexity, function, and adaptive capacity of multiple physiological systems in older healthy adults, when compared with Tai Chi naïve and novice (≤ 6 months training) Tai Chi practitioners**  ***Hypotheses*** *Compared to Tai Chi naïve and novice Tai Chi practitioners:*  *H.3.a) Long-term Tai Chi practitioners will exhibit higher levels of complexity across all measured physiological systems;*  *H.3.b) Long-term Tai Chi practitioners will exhibit higher levels of physical and cognitive function;*  *H.3.c) Long-term Tai Chi practitioners will exhibit higher levels of adaptive capacity;*  *H.3.d) The magnitude of the effects of long-term Tai Chi training on physiological complexity, function and adaptive capacity in healthy older adults will be positively correlated with age.*  **Specific Aim #4: To determine cross-sectionally if age is associated with greater complexity, function, and adaptive capacity of balance and gait in young healthy adults, when compared with to older adults**  ***Hypotheses*** *Compared to older adults and a young adult comparison group:*  *H.3.a); The magnitude of physiological complexity, function and adaptive capacity will be positively correlated with age.*  *H.3.b) Young adults will exhibit higher levels of adaptive capacity of balance and gait.* |

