### Statistical Considerations

| ***Sample Size Justification:*** Our analysis will be based on a longitudinal regression analysis in which we do not have an estimate of the within-participant correlations. In the worst case, the two follow-up measures provide no more information than a single follow-up, and the power calculation is equivalent to that for a simple t-test. With 30 participants in each group, we would have 50% power to detect an effect size of 0.52 (i.e., the sample size provides 50% sensitivity to detect a difference between groups .52 times the standard deviation of the outcome measure) and 80% power to detect an effect size of 0.74 for each of the main effects. Our primary hypothesis, however, is an interaction effect. Our sample size provides at least 50% power to detect an interaction effect size of 1.03, under this worst-case scenario. At the other extreme, if the two follow-up observations are independent, we will have 50% power to detect an interaction effect size of 0.72 and 80% power to detect an effect size of 1.03. The use of regression models further increases power by accounting for additional sources of variability. In our heart failure study, the mean difference in MSE change between Tai Chi and control was 2.26, which translates to an effect size of 1.2. Preliminary COP data from our Tai Chi for osteopenia study showed a similar effect. Therefore, we think changes of this magnitude will likely be present in the proposed study and our study has adequate power.  For Study Aim 3, we will in essence be comparing the 30 tai chi experts to the 60 novices. After adjusting for the effect of age, we will have 80% power to detect a difference between naïve and tai chi experts of approximately 0.65 times the residual error.  For Study Aim 4, we will be comparing the baseline COP and balance measures in the various age categories (15 participants age 25-35, and 20 participants in each of the older groups). This sample will provide at least 82% power to detect a difference between the young group and the average of the older groups equal to the within-group standard deviation.  ***b. Data Analysis***  *Aim 1*: We are interested in comparing the change over time in the Tai Chi students versus the controls. The primary analysis will use an intention-to-treat paradigm, i.e., participants will be evaluated on the basis of group assigned by randomization without regard to subsequent adherence. Since this is a pilot study, we will not impute values for missing data; however, the statistical models we are using will include all available data. We recognize that some participants may drop out before the follow-up evaluation and that some outcome measures may not be evaluable for some participants. We will make no adjustment for multiple testing. A secondary ‘per-protocol’ analysis will be limited to participants who were compliant (attended 70% of classes and completed at least 70% of home sessions).  Our primary analysis will employ linear mixed effects regression models that examine change over time (i.e., slope) for each outcome measure (i.e., the complexity measures, MSE and detrended fluctuation analysis) for each of the systems (i.e., heart rate, balance and gait). The models will incorporate a random intercept and a random slope for each participant. The models will be of the form:  ****  for individual  in treatment group  where the random intercept , the random slope , and the residual error . The focus of the primary analyses is on , which evaluates whether treatment is associated with the slope over time.  We will also conduct sensitivity analyses that incorporate additional covariates into the models, including age, gender, baseline physical and mental health, BMI, expectancy, and exercise behavior. We are particularly interested in examining age with a focus on assessing whether age substantially reduces the variability of the random effects, i.e., whether it explains a substantial proportion of between-person variability in baseline complexity and slope.  Analyses of secondary outcomes will follow the same general analytic approach. We will use mixed effects models to examine the effects of Tai Chi training over time on physical and cognitive function (exercise capacity, balance, upper and lower extremity strength, cognitive function, and quality of life) and adaptive capacity (change in heart rate, change in COP displacement, change in stride variability).  *Aim 2*: We hypothesize that function and adaptive capacity are associated with complexity. We will first examine the association between complexity measures and function/adaptive capacity at baseline. We will calculate Pearson correlation coefficients between the complexity measures (MSE and detrended fluctuation analysis) and the measures of function/adaptive capacity. To examine the independent association between complexity and function/adaptive capacity, we will fit ordinary least squares regression models using the function/adaptive capacity measures as the dependent variable. Independent variables will include age and sex as well as any other baseline characteristics associated with the function variable. We will add the complexity measure to this model and evaluate the Wald test and the change in R^2^.  We will also investigate whether changes in complexity are associated with changes in function/adaptive capacity. We will fit linear regression models with change in function/adaptive capacity as the dependent variable and change in complexity as the independent variable of interest. Since we will have 2 observations per participant (change at 3 months and change at 6 months), we will use generalized estimating equations methods (GEE) to account for the within-person correlation. Independent variables will include the measure of function/adaptive capacity at baseline, age, sex, treatment group and time (3 vs. 6 month).  Further, we hypothesize that complexity is the primary mediator of the association between Tai Chi and improvements in adaptive capacity. We will examine this using the approach recommended by Judd and Kenny.^193^ For example, to examine whether multi-scale entropy of balance mediates the effect of Tai Chi on center of pressure response to a dual cognitive task among the older participants, we will fit 3 regression models: regress MSE on Tai Chi use; regress COP response on Tai Chi; and regress COP response on MSE and Tai Chi use. The associations seen in these models determine the existence and strength of mediation.  Despite the implicit directionality of our hypotheses, all tests will be two-sided. We recognize that we are examining a moderate number of outcomes in this study. Since it is a pilot study and has limited power, we do not intend to adjust for multiple testing.  *Aim 3:* Our goal is to compare the complexity measures, function, and resilience to perturbations between tai chi experts and those with no tai chi training or only limited training. We expect responsiveness to decrease as a function of age among the tai chi naïve participants (i.e., both randomized groups combined). We hypothesize that tai chi experts will have a generally higher level of responsiveness, and that their responsiveness will decline with age at a slower rate than naïve or novice practitioners. To examine these questions, we will fit linear regression models to the baseline responsiveness measures for all participants:    where TC is an indicator variable for the tai chi experts.  is an estimate of the difference in responsiveness between tai chi experts at age 50,  is an estimate of the change in responsiveness per year for the novice group, and is the difference in rate of change between novices and tai chi experts.  We will fit a similar model to compare the tai chi experts to the naïve and novice groups using the 6-month data for the randomized patients and the baseline data for the tai chi experts. The group variable will be a categorical variable with 3 levels.  *Aim 4:* We will calculate sample means for each of the outcomes in each age group. We will use standard one-way analysis of variance to compare the four groups. If the overall test is significant, we will use Dunnett’s test to compare the young group to each of the older age groups. |

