### C. Subject Selection

| **Study population and recruitment procedures**  Identification of Arms 1 and 2 (Tai Chi naïve older adults)  A total of 60 healthy older adults (50-79 years old) will be recruited for our study. Recruitment will target community dwellers living within the Greater Boston area. Identification of potential study participants will include a variety of procedures that we have successfully employed in our prior studies. These include: 1) Posting study brochures and flyers in ambulatory clinics associated with BIDMC’s Department of General Medicine and Primary Care and Department of Gerontology (approximately 4,000 and 1,000 patients, respectively); 2) Direct referrals from providers in these and other clinics with whom we have a long-standing working relationship (e.g. [name] is the Chair of Gerontology and Drs. [name] and [name] are staff physicians in General Medicine); 3) Advertising in various publications including the Harvard Cooperative Program on Aging newsletter on healthy aging (disseminated 3 times a year to more than 9,500 older adults) and other local periodicals targeting older adults (e.g. *Fifty Plus Advocate, The Senior Times*), as well as on internet based resources such as Craig’s list; 4) BIDMC Syncope and Falls in the Elderly (SAFE) laboratory IRB approved database, whereby [name] provides names of potentially eligible participants who have offered to participate in SAFE lab studies; 5) Flyer placement in the communities surrounding the study’s network of Tai Chi schools (e.g., community bulletin boards, libraries).  Identification of Arm 3 (Tai Chi Expert Group)  A total of 30 healthy older adults (50-79 years old) each with over five years of tai chi practice will be recruited for our study. Recruitment will target tai chi experts living within the Greater Boston area. Potential study participants will be identified through advertisement and presentations given by PI and/or other co-investigator at Tai Chi schools.  Identification of Arm 4 (Young Comparison Group)  A total of 15 healthy young adults (25-35 years old) with no prior tai chi experience will be recruited for our study. Recruitment will target young adults living within the Greater Boston area. Potential study participants will be identified through advertisement and presentations given by PI and/or other co-investigator in the community.  5.2.2. Eligibility criteria  Arms 1 and 2: Recruitment will focus on healthy, relatively sedentary, older Tai Chi-naïve adults. Eligibility criteria will be based on screens conducted by study staff and confirmed by BIDMC GCRC nursing staff.  Arm 3 (Tai Chi Expert Group): Recruitment will focus on healthy tai chi experts with over five years of tai chi practice. Eligibility criteria will be based on screens conducted by study staff and confirmed by BIDMC GCRC nursing staff.  Arm 4 (Young Comparison Group): Recruitment will focus on healthy, relatively sedentary, young Tai Chi-naïve adults. Eligibility criteria will be based on screens conducted by study staff and confirmed by BIDMC GCRC nursing staff.  Arms 1 and 2 Inclusion criteria:  • Ages 50-79  • Living within the Greater Boston area  • Willing to adhere to 6 month Tai Chi training protocol  • Patients with a history of both solid and hematologic cancer (≥ 5 years of complete remission and who do not require chronic maintenance chemotherapy). Chronic use of hormonal agents such as aromatase inhibitors and GnRH analogs, however, are permissible with the understanding that these agents do not substantially alter the cardiovascular, autonomic, and postural control systems.  • Patients with prostate cancer (Stage I or II only)  • Patients with dermatological cancer that has been completely resected with no additional incidence.  Arm 3 (Tai Chi Expert Group) Inclusion criteria:  • Ages 50-79  • Have over five years of Tai Chi practice  • Patients with history of both solid and hematologic cancer (≥5 years of complete remission and who do not require chronic maintenance chemotherapy). Chronic use of hormonal agents such as aromatase inhibitors and GnRH analogs, however, are permissible with the understanding that these agents do not substantially alter the cardiovascular, autonomic, and postural control systems.  • Patients with prostate cancer (Stage I-II)  • Patients with dermatological cancer that has been completely resected with no additional incidence.  Arm 4 (Young Comparison Group) Inclusion criteria:  • Ages 25-35  • Living within the Greater Boston area  • Patients with a history of both solid and hematologic cancer (≥ 5 years of complete remission and who do not require chronic maintenance chemotherapy). Chronic use of hormonal agents such as aromatase inhibitors and GnRH analogs, however, are permissible with the understanding that these agents do not substantially alter the cardiovascular, autonomic, and postural control systems.  • Patients with prostate cancer (Stage I or II only)  • Patients with dermatological cancer that has been completely resected with no additional incidence.  Exclusion Criteria:  • Chronic medical conditions, including: cardiovascular disease (myocardial infarction, angina, atrial fibrillation, or presence of a pacemaker), stroke, respiratory disease requiring daily use of an inhaler, diabetes mellitus, malignancies (patients with diagnosis of active cancer < 5 years ago requiring ongoing chemotherapy or use of cytotoxic agents), neurological conditions (e.g., seizure disorder, Parkinson’s, peripheral neuropathy), or other neuromuscular or musculoskeletal (requiring chronic use of pain medication) disease  • Acute medical condition requiring hospitalization within the past 6 months  • Self-reported (current) smoking or alcohol/drug abuse  • Uncontrolled Hypertension (resting SBP > 160 or DBP > 100mm Hg)  • Abnormal heart rate (resting HR > 100 bpm; <50bpm)  • Abnormal ECG (supraventricular tachyarrhythmia, atrial fibrillation, significant ST wave abnormality, 2^nd^ and 3^rd^ degree heart block)  • Pregnancy  • Current use of prescription medications including cardio- or vaso-active drugs and medications that can affect autonomic function including Beta agonists and antagonists, drugs with anticholineric properties (e.g. tricyclic antidepressants or anti psychotics), and cholinesterase inhibitor^[[1]](#footnote-1)^  • Self-reported inability to walk continuously for 15 minutes unassisted^[[2]](#footnote-2)^  • Regular Tai Chi practice within past 5 years‡‡  • Regular participation in physical exercise on average 4 or more times per week‡‡  Arms 1 and 2 Recruitment, enrollment and randomization procedures  Potential participants who learn about our prospective study from brochures, referrals, or advertisements will be directed to call the study coordinator, who will conduct an initial eligibility screen by telephone, and schedule potentially eligible individuals for a visit at the BIDMC Clinic Research Center (CRC) for further screening. The coordinator will also discuss the randomization process and emphasize the 6 month commitment for those randomized to Tai Chi. Phone screen eligible individuals will be asked to visit at least one Tai Chi school prior to the on-site CRC screening visit. At the end of our initial phone screen, all participants will be informed about the Syncope and Falls in the Elderly (SAFE) Laboratory Research Recruitment Repository Database, and if they agree, their contact information will be given to [name]. [name] is the director of the SAFE Lab, PI of the Research Recruitment Repository Database, and a co-investigator on this study. Prior to baseline testing, individuals will undergo formal consenting following BIDMC and NIH guidelines. Following baseline testing, participants will be randomly assigned to one of two interventions, Tai Chi or wait list control.  Our study statistician, [name] will be responsible for randomization procedures. We will stratify participants by age (50-59, 60-69, 70-79), generate treatment assignments using a permuted-blocks randomization scheme with randomly-varying block sizes, and seal the treatment assignments in opaque, sequentially numbered envelopes for each stratum. The use of stratification will limit the potential for confounding by age. Upon randomization, study staff will enter the participant’s name and medical record number into a randomization log. All randomization materials will be stored in a locked file, with access limited to non-blinded study personnel.  Arm 3 (Tai Chi Expert Group) Recruitment and enrollment procedures  Potential participants who learn about our prospective study from referrals or advertisements will be directed to call the study coordinator, who will conduct an initial eligibility screen by telephone, and schedule potentially eligible individuals for a visit at the BIDMC Clinic Research Center (CRC) for further screening.  Arm 4 (Young Comparison Group) Recruitment and enrollment procedures  Potential participants who learn about our prospective study will be directed to call the study coordinator, who will conduct an initial eligibility screen by telephone, and schedule potentially eligible individuals for a visit at the BIDMC Clinic Research Center (CRC) for further screening.  Remuneration  Arms 1 and 2: All parking expenses associated with CRC visits will be paid for by the study. Eligible and consented participants who complete outcome assessments will be paid $100 at study midpoint (3 months), and $100 at study endpoint (6 months) with a maximum compensation of $200. Participants who complete the screening process but are not eligible to participate further will receive $50.Tuition for all Tai Chi training over the 6-month study period will be paid for by the study. Participants in the control group will also be offered 3 months of free Tai Chi training at the completion of the study at their choice of school within our network.    Arm 3 (Tai Chi Expert Group) Remuneration:  All parking expenses associated with CRC visits will be paid for by the study. Eligible and consented participants who complete outcome assessments will be paid $200 following single visit.  Arm 4 (Young Comparison Group) Remuneration:  All parking expenses associated with CRC visits will be paid for by the study. Eligible and consented participants who complete outcome assessments will be paid $50 following single visit. |

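### Randomisation is stratified by age, but the Aim 1 primary model appears to contain no age terms; some precision is lost wherever age predicts the rate of change

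*Protocol*

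**What the plan says.** **Allocation** (Protocol, C. Subject Selection, randomization procedures for Arms 1 and 2): "We will stratify participants by age (50-59, 60-69, 70-79), generate treatment assignments using a permuted-blocks randomization scheme". The stated purpose is: "The use of stratification will limit the potential for confounding by age".

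**Primary analysis** (Protocol, Statistical Considerations, Data Analysis, Aim 1): a linear mixed model for each complexity outcome. "The models will incorporate a random intercept and a random slope for each participant". The parameter of interest is the one "which evaluates whether treatment is associated with the slope over time". Secondary outcomes follow the same general approach.

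**Age in Aim 1**: it enters only in a later paragraph. "We will also conduct sensitivity analyses that incorporate additional covariates into the models, including age, gender". That paragraph singles age out, with a focus on "assessing whether age substantially reduces the variability of the random effects", meaning the variation between people in baseline complexity and in slope.

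**Age in the hypotheses** (B1, H.1.d): the size of the Tai Chi effect "in healthy older adults will be positively correlated with age".

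**Power**: the sample size paragraph falls back on a simple t-test as the worst case. It then says that the primary hypothesis is an interaction, with 50% power at 1.03 in the worst case, and 50% at 0.72 and 80% at 1.03 if the two follow-ups are independent.

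**The concern.** When allocation is balanced within strata of a factor, variation due to that factor is largely removed from the difference between arms. A model that leaves the factor out still counts that variation as error. Its standard error is then larger than the true sampling variation of the estimate, so the test is conservative and the interval wider than necessary.

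Here the design balances on age, the background section argues that complexity falls with age, and the Aim 2 regressions and the Aim 3 model all carry age. The Aim 1 primary model seems to be the exception. The sample size paragraph also says that regression raises power by accounting for further sources of variability, but the source the design was built around is left to sensitivity analyses.

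At stake is precision in a 60-person pilot that is meant to supply preliminary effect sizes, and whose primary interaction test has only 50% power at 1.03 in the protocol's own worst case. There is no inflation of the false-positive rate.

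**Working it through.** **Inputs from the protocol.** 30 per arm; visits at 0, 3 and 6 months; two-sided tests; effect sizes 0.52, 0.74, 0.72 and 1.03. **Assumed.** Alpha 0.05 (not stated), and R², the share of variance in observed per-participant slope that age explains (not given; 2% to 20% shown).

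**1. The protocol's figures reproduce** (noncentral t).
- Main effect: SE = √(2/30) = 0.258. Power is 50.8% at 0.52 and 80.5% at 0.74 (stated 50% and 80%).
- Interaction, worst case: SE = 2√(2/30) = 0.516. At 1.03 the noncentrality is 1.03/0.516 = 1.99, giving 50.0% (stated 50%).
- Interaction, independent follow-ups: SE = 0.516/√2 = 0.365. Power is 49.8% at 0.72 and 79.9% at 1.03 (stated 50% and 80%).

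None of these takes credit for age, so omitting age does not make them too high.

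**2. Does an age main effect help the slope test?** The planned model was simulated with 60 participants, three age strata, 1:1 allocation and 250 to 400 runs per scenario. Assumed values: intercept SD 1, slope SD 0.5 per 6 months, residual SD 0.5, true slope difference 0.6.

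| Age explains | SE, no age | SE, age main effect | Power, each |
|---|---|---|---|
| 25% of intercept variance | 0.2248 | 0.2247 | 74.0% / 74.0% |
| 49% of intercept variance | 0.2223 | 0.2224 | 74.0% / 74.0% |
| 25% of intercept variance, 15% dropout | 0.2379 | 0.2379 | 68.4% / 69.2% |

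It does not. The random intercept already absorbs age differences in level. With complete data this result does not depend on the assumed variances.

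**3. Does age by time help?** Only if age predicts slope. Let age explain 25% of true slope variance. With visits at 0, 3 and 6 months and residual SD 0.5, true slope variance is 0.25/(0.25 + 0.5) = one third of observed slope variance, so this is about 8% of observed slope variance. The SE falls from 0.2224 to 0.2129, a ratio of 0.957, and power goes from 76.4% to 78.4%. The formula in step 4 gives √(1 − 0.083) = 0.957, which agrees.

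Under the null in the same setting (400 runs), the model without age had mean SE 0.2240 against an empirical SD of 0.2119 and rejected 4.0% of the time; with age by time it rejected 5.0%. The Monte Carlo error is about 1 point, so the rejection rates only suggest conservatism.

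**4. Range on the protocol's own interaction size.** SE ratio = √(1 − R²). Noncentrality at 1.03, worst case = 1.99/√(1 − R²).

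| R² (assumed) | SE ratio | Noncentrality | Power with age by time |
|---|---|---|---|
| 0% | 1.000 | 1.99 | 50% |
| 2% | 0.990 | 2.01 | 51% |
| 5% | 0.975 | 2.05 | 52% |
| 10% | 0.949 | 2.10 | 54% |
| 20% | 0.894 | 2.23 | 59% |

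Without age in the model, power at this point stays near 50% throughout, because the expected estimate sits about at the critical value of the unadjusted test. Under the variances in step 2, an R² of 20% would need age to explain about 60% of true slope variance (0.20 × 3), so the lower rows are the more plausible ones.

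**The case against.** The strongest reply is that the primary test is a difference in slopes. The evidence in the background section that age matters is cross-sectional and concerns level, which the random intercept takes out. That stands: without an age-slope relation the loss is zero.

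H.1.d does not settle the matter. It says that the treatment effect varies with age, and its direct test is treatment by age by time, not age by time. H.1.d and the planned check on random-slope variance make an age-slope link plausible, but the protocol treats it as an open question and puts no number on it.

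The protocol also already plans age-adjusted models. What is left is which model is called primary, in a pilot with no multiplicity adjustment and an error in the safe direction. That also stands, and it keeps the point minor. It does not remove the mismatch, because the primary estimate still comes from the model that ignores the stratification.

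Finally, the model equation did not survive in the text available to me. The absence of age is inferred from its being listed among additional covariates. An SAP, not at hand, may already include it.

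A reader might infer that the primary standard errors are too wide, and power lost, for every Aim 1 outcome. The documents do not support that: it holds only for outcomes where age predicts change, and no such correlation is reported. Nor should the loss be measured against 0.74, which is the protocol's main-effect size; the protocol names the interaction as its primary hypothesis.

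**Conclusion.** The point holds in a limited, conditional form. Allocation is stratified by age, and as far as the text shows the Aim 1 primary model has no age terms. Where age predicts the rate of change, the treatment-by-time test is mildly conservative and somewhat imprecise. Where age affects only level, there is no loss.

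The likely size is small: a standard error 1% to 5% larger than necessary, and about 1 to 4 power points at the worst-case interaction size, if age explains 2% to 10% of observed slope variance. At 20% these become about 11% and 9 points. These figures rest on an assumed R², alpha of 0.05 and complete data. The stated power is not overstated, and validity is not at risk. Severity: minor.

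**What to change.** In Statistical Considerations, Aim 1, prespecify age and age by time as fixed effects in the primary model for all Aim 1 outcomes, using either the randomisation stratum or centred continuous age. Both terms are needed, since the main effect alone leaves the slope contrast unchanged. Retain the model without age as the sensitivity analysis. If the SAP already does this, align the protocol wording with it.

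The cost is a change of wording, made before unblinding, and 2 degrees of freedom (continuous age and its product with time) to 4 (two stratum indicators and their products with time). No change to sample size or data collection is needed.
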